#### Self-report measures

Researchers will administer pre-testing questionnaires during the initial contact with participants after they have given consent to participate in the trial, before group assignment (as described above). Follow-up assessments will be made at 3-month intervals for the primary outcome measure and for secondary outcome measures assessing violence, intimate partner violence, and anger; at 12-month intervals for the secondary outcome measures assessing categorically defined ASPD and rates of desistance; and at 6-month intervals for all other secondary outcome measures. Assessments will continue for the duration of the 12-month treatment and for 12 months post-treatment. Self-report measures of violence, offending behaviour, substance misuse, self-harm, and suicidality, as well as general health and wellbeing, service satisfaction, and engagement, will be collected.

*Violence* will be measured by the MacArthur Community Violence Screening Instrument [25, 81]. This measure assesses the presence, severity, and frequency of violent behaviours and is one of the few instruments available to differentiate between general aggression and specific interpersonal violence [82].

*Intimate partner violence* will be measured by the Short Form of the Revised Conflict Tactics Scales. This measure includes scales to measure physical assault, psychological aggression, and sexual coercion against a partner in a dating or marital relationship.

*Anger* will be measured by the State-Trait Anger Expression Inventory-2 (STAXI-2) [83, 84]. The STAXI-2 is a psychometrically robust questionnaire [85] designed to assess the experience, expression, and control of anger, which commonly drives aggression.

*Alcohol use*, which has been strongly associated with aggression and offending [86], will be measured by the Alcohol Use Disorders Identification Test (AUDIT) [85, 87]. The AUDIT is widely used as an alcohol use screening measure. It assesses three aspects of drinking: quantity and frequency, indicators of dependence, and adverse consequences suggesting harmful use.

*Drug use*, which is similarly linked to aggression and offending [88], will be measured by the Drug Use Disorders Identification Test (DUDIT) [89], which assesses frequency of use, indicators of dependence, and adverse consequences suggesting harmful use. The DUDIT has several advantages over other instruments, including a brief administration time (5 min) and its focus on recent use and consequences.

*Self-harming behaviours*, an indicator of impulsivity and a target of MBT, will be measured by the Self-Harm Inventory [90], a widely used measure that yields a severity of self-harm score based on the frequency of a wide range of impulsive behaviours.

*Suicidal behaviour*, a further complication of offending behaviour with ASPD [91], will be measured by the Suicidal Behaviours Questionnaire-Revised [92]. This instrument assesses four different dimensions of suicidality, including frequency of suicidal ideation and threat of suicide attempt.

*Health-related quality of life* will be measured by the EQ-5D-5L [93, 94]. The EQ-5D-5L is a standardized instrument for use as a measure of health outcome that is applicable to a wide range of health conditions and treatments. In this study, it will be used to provide a generic measure of health for both clinical and economic appraisal.

*Mental health status* will be measured by the Symptom Checklist-90 – Revised (SCL-90-R) [95]. The SCL-90-R assesses psychological distress in terms of nine primary symptom dimensions, including depression, anxiety, hostility, and paranoid ideation—all potential drivers of aggression.

*Personality dysfunction* will be measured by the Personality Inventory for DSM-5 – Brief Form (PID-5-BF) [96]. This 25-item personality trait assessment scale assesses negative affect, detachment, antagonism, disinhibition, and psychoticism and will provide a means of assessing change in the trait domains that are most prominent in ASPD.

*Categorically defined ASPD* will be measured by the ASPD module of the SCID-II, to assess whether MBT produces remission in ASPD diagnostic status.

*Mentalizing capacity* will be evaluated by the 16-item Brief Reflective Functioning Questionnaire [97] to assess whether MBT’s proposed mechanism of change is in line with any symptomatic improvements.

*Rates of desistance* will be measured by the Redemption and Condemnation Self-Narrative Scale version 2 to assess whether MBT increases rates of desistance in the participants.

#### Clinician-rated measures

Clinicians (therapists, Assistant Psychologists, and Offender Managers) will use the Service Engagement Scale [98] to determine the level of engagement of participants, as rated on four subscales: availability, collaboration, help-seeking, and treatment adherence.

#### Economic evaluation

Health economic analysis will be conducted by King’s Health Economics at the Institute of Psychiatry, Psychology and Neuroscience, King’s College London, and will explore the relative costs and cost-effectiveness of MBT+PAU versus PAU. Although there is a preference for economic evaluations carried out on NHS services to take an NHS and personal and social services cost perspective, as recommended by NICE [99], in this case our primary analysis will take a wider societal perspective, including all healthcare, social and personal services, voluntary sector services, costs to the criminal justice sector, including probation, and the costs resulting from any crimes committed. The wider perspective is relevant and valid here because the interventions being compared are delivered in a criminal justice setting and the hypothesized impact will fall across both healthcare and criminal justice. A secondary analysis will consider the NHS/personal and social services costs only. Data on MBT contacts will be collected directly from sites, to avoid participants revealing their group allocation to the researchers. Data on the use of all other services, including PAU, will be collected in interviews using the Secure Facilities Service Use Schedule [100]. This instrument has been adapted to the current study population to ensure comprehensive coverage and face validity. Information on criminal activity will be extracted from police records. The cost of the trial interventions will be calculated through a detailed micro-costing (or bottom-up) approach using standard costing methodology [101], which will involve estimation of the indirect time spent on individual cases, including preparation, meetings, telephone calls, and supervision, as well as detailed recording of direct face-to-face contact. Other unit costs will be sourced from routine sources for the unit cost year 2017–2018 [102–104].

#### Follow-up assessment

Follow-up assessments will be conducted at 3-month intervals for 24 months post-randomization. Primary outcome measures will be collected every 3 months and secondary outcome measures every 6 months. Table 1 shows a detailed outline of the planned measures at each follow-up point throughout the trial.

**Table 1 Tab1:** Schedule of assessment administration for a randomized controlled trial of mentalization-based treatment for antisocial personality disorder

	Study period										
	Enrolment	Allocation	Post-allocation								
			T1	T2	T3	T4	T5	T6	T7	T8	T9
**ENROLMENT**											
Eligibility screen	x										
Informed consent	x										
Allocation		x									
**INTERVENTION**											
MBT			x	x	x	x	x				
PAU			x	x	x	x	x				
**ASSESSMENTS**											
**Questionnaires—participant**											
Overt Aggression Scale – Modified			x	x	x	x	x	x	x	x	x
EQ-5D-5L			x		x		x		x		x
Symptom Checklist-90–Revised Short Form			x		x		x		x		x
Alcohol Use Disorders Identification Test			x		x		x		x		x
Drug Use Disorders Identification Test			x		x		x		x		x
State-Trait Anger Expression Inventory			x	x	x	x	x	x	x	x	x
MacArthur Community Violence Screening Instrument			x	x	x	x	x	x	x	x	x
Short Form of the Revised Conflict Tactics Scales			x	x	x	x	x	x	x	x	x
Self-Harm Inventory			x		x		x		x		x
Suicidal Behaviours Questionnaire – Revised			x		x		x		x		x
Secure Facilities Service Use Schedule			x		x		x		x		x
Personality Inventory for DSM-5-Brief Form			x		x		x		x		x
SCID-II, ASPD Module			x				x				x
Brief Reflective Functioning Questionnaire			x		x		x		x		x
Redemption and Condemnation Self-Narrative Scale version 2							x				x
**Questionnaires—clinician**											
Service Engagement Scale					x		x		x		x
National Probation Resources, Evaluation and System Schedule			x		x				x		x
**Police and health data**											
Police records			x		x		x		x		x
Health records			x		x		x		x		x

### Data management

#### Collection

Outcome measures data will be recorded using the Patient Owned Database (POD), an internet-based high-security data collection and management software. POD automatically scores and transmits the data to the data-analytic site without human interference, reducing the risk of data entry error. Once entered, the data will be exported and cleaned by the CTU ready for analysis by the trial statistician. In line with a data sharing agreement with the NPS and UCL Data Protection Policy, participants’ personal data will be collected and securely stored in password-protected files only accessible by members of the research team during the course of the study. At the end of the trial, all data will be archived in a safe and secure off-site location.

#### Auditing

The quality of data will be routinely monitored by the Research Manager throughout the duration of the trial. In addition, data quality will be monitored quarterly by an independent audit group, which will be responsible for reviewing data collection and completeness rates.

### Statistical analysis

All planned statistical analyses will be specified in a Statistical Analysis Plan that is agreed prior to unblinded information being made available to the trial statistician. Primary analyses will be on an intent-to-treat basis, with per-protocol (all participants who were randomized, who met inclusion/exclusion criteria, and who attended at least 35% of planned meetings with their parole officer) analyses undertaken as secondary. The characteristics of the treatment groups will be described at baseline. Preliminary analysis will investigate the pattern of missing follow-up data.

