### Planned interventions

Implementing standard PAU or PAU supplemented with MBT will not require alteration to usual pathways (including use of any medication), and these will continue for both trial arms.

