#### PAU

Participants randomized to receive PAU will remain under the supervision of the NPS for the duration of their licence or community sentence. PAU is a well-specified and stringently monitored standard procedure used in the management of offenders under community supervision. It consists of regular contact with a designated Offender Manager for the duration of the offender’s licence or sentence, and includes referral for additional interventions as indicated in Ministry of Justice guidance. PAU participants will be free to be referred by their Offender Manager for any locally available treatment (except MBT) designed to reduce reoffending (e.g. anger management programmes, substance misuse interventions). Provision of these interventions is not uniform across the UK but dependent on local availability; in some areas, there may be no targeted interventions available. Unlike MBT, none of the interventions that participants may receive under PAU involve targeting the capacity to envision mental states more accurately. Details of services accessed under PAU will be documented by the SOM to facilitate economic data collection and evaluation. Additional site-specific strategies (e.g. separate supervision groups) will ensure that MBT principles and practice do not directly influence the management of participants randomized to PAU. PAU will last for 12 months, after which participants who still have time remaining on their licence or community sentence will remain under the supervision of the NPS for the duration. Participants whose licence expires during the trial period may remain under the NPS on a voluntary basis to complete the 12-month period.

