#### PAU supplemented with MBT-ASPD

The treatment intervention is a 1-year programme of group and individual sessions of MBT-ASPD. Participants randomized to MBT-ASPD receive weekly group therapy for 75 min and monthly individual therapy for 50 min. Each MBT-ASPD group is run by two trained MBT clinicians and contains a maximum of eight participants, using an ‘open’ rolling entry group, with new participants joining as others leave. The group process enables participants to challenge each other about their understanding of current self-identified critical interpersonal experiences and focuses particularly on elaborating the mental state background of interactions characterized by conflict that might normally trigger aggression. The content of the group therapy sessions is steered by the clinicians toward encouraging the participants to talk about their mental states related to recent violent incidents by linking their actions to a broader range of their current subjective and emotional experience (i.e. to ‘mentalize’ them). A monthly 50-min individual session provides an opportunity for participants to address personal issues that have occurred in the group. Many participants find it more difficult to talk in front of other members of the group about the relationship difficulties they experience in their external lives, and may use the individual sessions to do this too. Both group and individual sessions focus on identifying thoughts and feelings associated with aggressive impulses, with particular emphasis on understanding emotional cues, recognizing emotions in oneself and others, understanding others’ experiences in relation to one’s own, and clarifying threats of loss to mentalizing in the context of life experiences, both currently and historically.

All participants randomized to this arm of the study have an allocated clinician. Staff providing MBT sessions are chartered health professionals with a core clinical training background (e.g. clinical psychology, nursing, medicine) who have undergone an MBT training course. Where possible, recently trained clinicians are paired with an experienced clinician to provide group MBT.

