#### Mediators of outcomes

We will test the following as mediators (if there is a significant difference between arms in the mediating variable): alcohol use (AUDIT score); drug use (DUDIT score); mood (scores on the anxiety and depression subscales of the SCL-90-R); mentalizing (Brief Reflective Functioning Questionnaire score).

We will also test the proportion of MBT planned sessions attended as a post-baseline effect modifier (as it is only collected in the MBT arm).

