Aggressive antisocial behaviour has been chosen as the primary outcome for this trial, in light of it being a core feature of ASPD, an indicator of emotional wellbeing, and a frequent cause of grounds for arrest. A range of secondary outcomes have also been chosen in order to evaluate MBT’s possible impact on the wide range of symptomatology and health outcomes experienced by individuals with ASPD, including impulsivity, offending behaviour, alcohol and substance misuse, self-harm and suicidality, and general health and wellbeing. The MOAM trial will also provide accurate information about the services accessed under PAU. A comprehensive cost-effectiveness evaluation will be undertaken to examine both costs offset and costs saved in relation to having received MBT or PAU. Thus, the trial will provide unprecedented data not only on the clinical effectiveness and cost-effectiveness of MBT-ASPD, but also on the clinical effectiveness and cost-effectiveness of the usual services available to this group while on probation. Furthermore, the trial will analyse offender referral information to identify trends, calculate the size of the population likely to benefit from an intervention for ASPD, and make recommendations about treatment groupings and targeting of services.

Information to date suggests that the trial protocol detailed above is acceptable to all the sites and that recruitment, data collection, and training are feasible in all locations. Preliminary data on participant engagement indicate that, of participants randomized to MBT, an average of 55–65% attend group MBT sessions. Preliminary data indicate that one third of participants drop out at some point following randomization, entirely consistent with attrition rates reported in other studies involving treatment for offenders and patients with personality disorders [70–72]. For participants who drop out, the average length of engagement with the trial is 3–6 months; the most common reasons for dropout thus far are lack of motivation (58%), recall to prison (35%) and clinicians’ discretion due to repeated non-attendance of MBT sessions (7%).

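### The secondary per-protocol set is defined by attendance at probation meetings, not MBT sessions, so its result cannot be read as the effect of receiving MBT

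*Protocol article*

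**What the plan says.** The Statistical analysis section makes intent-to-treat primary and per-protocol secondary ("Primary analyses will be on an intent-to-treat basis, with per-protocol"). A man enters the per-protocol set if he was randomised, met the eligibility criteria and is one "who attended at least 35% of planned meetings with their parole officer". No other attendance condition is given.

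Four other sections bear on what that rule measures:

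- **PAU**, on probation as usual: "It consists of regular contact with a designated Offender Manager for the duration of the offender’s licence or sentence".
- **Planned interventions**, on usual care under either allocation: it "will not require alteration to usual pathways (including use of any medication), and these will continue for both trial arms".
- **PAU supplemented with MBT-ASPD**, on the tested treatment: "Participants randomized to MBT-ASPD receive weekly group therapy for 75 min and monthly individual therapy for 50 min". These sessions are run by MBT clinicians.
- **Mediators of outcomes**, on MBT attendance: "We will also test the proportion of MBT planned sessions attended as a post-baseline effect modifier". The section notes that this variable exists in the MBT arm only.

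The Sample size section also plans descriptive counts of people who never attended and of sessions attended, as measures of treatment acceptability.

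**The concern.** A per-protocol analysis is normally read as the comparison among people who took the treatment as planned. Here the adherence condition concerns the component that both arms share, and it is silent on the component that differs. A result reported under this label invites a reading that the set cannot support: a null result could be quoted as showing that MBT fails even when received, and a positive one as confirming efficacy in those who received it. The article addresses policymakers and commissioners, so the label matters.

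Poor uptake of MBT is foreseen. The article plans to count people who never attended, and the Discussion lists repeated non-attendance at MBT sessions among the reasons for dropout (7%).

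**Working it through.** **1. What does not depend on the rule.** The plan's own figures come first. Inputs from the Sample size section: difference 10, SD 20, two-sided 5%, power 90%, ICC 0.05 in the MBT arm, attrition 37%.

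- Without clustering: n = 2 × [20 × (1.960 + 1.282) / 10]² = 84.06, so 85 per arm.
- Clustering in the MBT arm only: n = 84.06 × (1 + DE)/2, with DE = 1 + (m − 1) × 0.05. The cluster size m is not stated. Assuming m = 6, DE = 1.25 and n = 84.06 × 1.125 = 94.6, so 95 per arm. With m from 5 to 7 the result is 93 to 97.
- Attrition: 95 / (1 − 0.37) = 150.8, so 151 per arm and 302 in total.

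The stated 95, 151 and 302 reproduce. The per-protocol rule enters none of these steps, nor the intent-to-treat model.

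**2. Which component the rule measures.**

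| Component | MBT arm | PAU arm | In the per-protocol rule? |
|---|---|---|---|
| Probation meetings | yes | yes | yes, at least 35% |
| MBT group sessions, weekly | yes | no | no |
| MBT individual sessions, monthly | yes | no | no |

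The term parole officer appears only in this rule; elsewhere the article speaks of an Offender Manager. I take them to be the same role. In either case it is not an MBT session.

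**3. The rule applied to men allocated to MBT** (constructed cases, all eligible).

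| MBT sessions attended | Probation meetings attended | In the set? |
|---|---|---|
| none | 35% or more | yes |
| all | 34% | no |
| all | 35% or more | yes |
| none | 34% | no |

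The first two rows are the problem. Membership follows probation attendance alone, whatever the MBT exposure.

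**4. Whether the size can be computed.** Let q be the share of MBT-arm men in the set who attended no MBT. Assume they gain nothing and the others gain Δ on average. Leaving selection aside, the expected contrast is (1 − q)Δ. It runs from Δ at q = 0 to zero at q = 1. Finding q needs MBT attendance among men who reached 35% of probation meetings. The article gives neither that figure nor the number who reached the threshold, so it does not narrow the range. Partial attendance and selection by probation attendance would also matter, and they are equally unquantified.

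**The case against.** The best defence is symmetry. A probation-contact rule can be applied in the same way to both arms, whereas an MBT-session rule has no counterpart under PAU, and a plain subset of MBT attenders would be a self-selected group compared with all PAU men. That stands as an argument against a naive MBT-based subset. It does not turn the present set into one of men who received MBT, and the article does not offer symmetry as its reason. Selection after randomisation also remains possible under the probation rule, as it does for per-protocol sets generally.

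The article also nowhere says that the per-protocol analysis is meant to show whether MBT works when received. That is correct. The point here is what the label will be taken to mean and what the set cannot deliver.

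Nor is MBT exposure ignored: it is counted descriptively and tested as a post-baseline effect modifier. Both are useful, but neither changes who is in the per-protocol set. Finally, an SAP that is not shown may define the set differently. The article did not leave the matter open, however: it states a rule with a numerical threshold. If the SAP differs, the two need reconciling.

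**Conclusion.** The point holds as one of definition. The set measures adherence to care common to both arms, keeps MBT-arm men with no MBT, and drops men who attended MBT but few probation meetings. It should be corrected. Because the analysis is secondary, the primary estimate and its power are untouched. The conclusion rests on the article's wording and on reading parole-officer meetings as ordinary probation contact.

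A reader might infer three stronger things that the article does not support:

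- **That the dilution can be read off the preliminary attendance figure.** The Discussion sentence beginning "Preliminary data on participant engagement indicate that, of participants randomized to MBT" goes on to give 55–65%. It does not say clearly whether this is a share of men or of sessions, and it describes men randomised to MBT, not those in the per-protocol set. The two would match only if probation and MBT attendance were unrelated. Lack of motivation (58%) and recall to prison (35%), the main dropout reasons, could plausibly lower both. The planned 10 points is also a between-arm difference, not a full-attendance effect.
- **That the attendance analysis under Mediators of outcomes is impossible to fit.** That section states no estimator. The interaction method is given under Moderators of outcomes, for other variables. A post-baseline variable seen in one arm can be handled by instrumental-variable or principal-stratum methods, and the choice is ordinary SAP content.
- **That differing licence lengths make the 35% denominator defective.** A percentage of planned meetings is a usual way to allow for differing schedules, and the PAU section lets men whose licence expires stay on voluntarily to complete 12 months.

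**What to change.** Before any unblinded information reaches the trial statistician:

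1. Define adherence by a pre-specified minimum share of planned MBT group and individual sessions, fixing the share and how the two session types are combined.
2. Estimate the effect of meeting that definition as a complier-average causal effect, with randomised allocation as the instrument, adjusted for baseline OAS-M and the minimisation factors (site, age band, probation order type, time remaining on probation). This keeps every randomised man in the comparison and avoids a naive subset.
3. If the probation-attendance set is kept, rename it as adherence to probation and state that it is not to be interpreted as efficacy of MBT when received.

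The cost is mainly wording in the protocol and SAP. The Economic evaluation section already has MBT contacts collected directly from sites, and the Trial status section says follow-up was still in progress. The sample size does not change. The downside is statistical: the complier-average estimate is less precise than the intent-to-treat one, and it needs an exclusion restriction, namely that allocation affects aggression only through meeting the attendance definition. Benefit from a few sessions below the threshold would breach it, so the SAP should state the assumption openly.
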